**Not applicable**

Study procedures will be conducted at UVM Buprenorphine Research Clinic, which has been the site of BUP research for the past 25 years. The clinic is located in our University Medical Center's outpatient building and is contiguous with our other research clinics for cocaine dependence and smoking cessation as well as our methadone clinic for which [name] is Director. IBT participants will visit the clinic every 2 weeks while receiving the IBT package described above. WLC participants will remain on the waitlist for their treatment of choice, though they will complete the same scheduled follow-up assessments as IBT participants. WLC participants who have not entered treatment by Week 24 will be offered the opportunity to cross over to IBT at that time, contributing additional within-subject data with which to evaluate the efficacy of the IBT intervention. The intake assessment will include a Drug History Questionnaire, ASI (McLellan et al., 1985), psychoactive substance dependence section of the DSM-5 (APA, 2013), Brief Symptom Inventory (Derogatis, 1993), Beck Depression and Anxiety Inventories (Beck et al., 1988, 1996), Michigan Alcoholism Screening Test (Selzer, 1971) and a Time-Line Followback of past-month use of opioids and other drugs (Sobell & Sobell, 1992). Participants will also complete a medical history, receive a brief physical exam, and provide a urine specimen (see *Biochemical monitoring*). Follow-up assessments will consist of abbreviated versions of the intake, will include urinalysis, and be administered monthly during the 6-month trial (i.e., at Weeks 4, 8, 12, 16, 20, and 24).

**Statistical Considerations:** Delineate the precise outcomes to be measured and analyzed. Describe how these results will be measured and statistically analyzed. Delineate methods used to estimate the required number of subjects. Describe power calculations if the study involves comparisons. Perform this analysis on each of the primary and secondary objectives, if possible.

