Side effects of buprenorphine: The side effects of buprenorphine include light-headedness, dizziness, sedation, lethargy, changes in sexual ability, nausea, vomiting, sweating, euphoria, constipation, respiratory depression, flushing of the face, skin itchiness or redness, darkening of the skin and/or swelling, bradycardia, headache, yawning, tearing, runny nose, muscle tremor, dilated or constricted pupil, restlessness, diarrhea, hypertension, hypotension, or potentially elevated liver enzyme levels (particularly among subjects with a history of hepatitis). The administration of the partial opioid agonist, buprenorphine, in individuals physically dependent on opioids should not result in acute toxicity because these individuals are tolerant to such drug effects. There also is a ceiling on the agonist effects of partial agonists; thus, the agonist effects of the partial agonist, buprenorphine, are considered to be safer than full agonists. Because buprenorphine is a partial agonist, it could also function as an antagonist and promote withdrawal symptomatology. We will administer buprenorphine in accordance with standard practice (see Methods) and, based on our previous experience in treating opioid-dependent individuals with this medication ([name] et al., 2009; [name] et al., 2013, 2015, 2016), we do not anticipate that buprenorphine-precipitated withdrawal or sedation will pose a problem.

Protection Against Risk: (1) To protect confidentiality, the guidelines stated in Title 42 of the Code of Federal Regulations, Part 2, "Confidentiality of Alcohol and Drug Abuse Records" will be followed. As stated in these regulations, subjects will be given a notice of federal confidentiality requirements (which will be included in the consent form). All records will be locked in file cabinets kept on site behind locked doors. Except for intake material, subjects' names (i.e., first and last names) will not be attached to the data forms. A central code/data base linking subject number with subject names will be kept, which will be available only to specified staff.

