**SUBJECT CHARACTERISTICS, IDENTIFICATION AND RECRUITMENT**

**Subject Selection:** Provide rationale for subject selection in terms of the scientific objectives and proposed study design.

Subjects will be adults with current opioid use disorder who are waitlisted for methadone or buprenorphine treatment

**Vulnerable Populations:** Explain the rationale for involvement of special classes of subjects, if any. Discuss what procedures or practices will be used in the protocol to minimize their susceptibility to undue influences and unnecessary risk (physical, psychological, etc.).

☒ **Not applicable**

**Number of Subjects:** What is the anticipated number of subjects to be enrolled at UVM/UVM Medical Center and in the case of a multi-center study, with UVM/UVM Medical Center as the lead, the total number of subjects for the entire study.

The anticipated number of subjects to be enrolled in the study is 100 (50 per experimental condition).

**Inclusion/Exclusion Criteria:** Eligibility and ineligibility criteria should be specific. Describe how eligibility will be determined and by whom. Changes to the eligibility criteria at a later phase of the research have the potential to invalidate the research.

Participants must be  $\geq 18$  years old, in good health, meet DSM-5 criteria for opioid use disorder and provide an opioid-positive urine at study intake. Consistent with our prior BUP studies, those with a significant psychiatric or medical illness that may interfere with consent or participation will be excluded, as will those who are pregnant or nursing. Those dependent on sedative-hypnotics will be excluded, due to the medical risks and notably low success rates with sedative-dependent opioid abusers (Stitzer & Chutuape, 1999). Intake information will be reviewed by the PI ([name]) and study physician ([name]), who will determine and document whether the participant is eligible and healthy to participate.

**Inclusion of Minorities and Women:** Describe efforts to include minorities and women. If either minorities or women are excluded, include a justification for the exclusion.

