## METHODS AND PROCEDURES

**Study Design:** Describe the research design, including a description of any new methodology and its advantage over existing methodologies.

We propose to conduct a Stage II randomized trial evaluating the efficacy of IBT using a larger sample of 200 waitlisted opioid-dependent adults and longer duration of evaluation. Participants randomly assigned to the IBT condition (n=100) will receive the above IBT intervention over a 24-week period with monthly assessments. Those randomized to WLC (n=100) will remain on the waitlist for their treatment of choice but complete the same monthly assessments. We hypothesize that IBT participants will demonstrate significantly greater illicit opioid abstinence relative to WLC participants. Additional outcomes will include IV drug use, other (non-opioid) drug use, retention, and several IBT-specific measures (e.g., BUP adherence, IVR utilization, patient satisfaction). WLC participants who have not entered treatment by the end of the study will be offered the opportunity to receive IBT at that time (described below). This study design feature will provide additional data with which to evaluate IBT effects beyond the initial randomized sample of 100 participants.

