**Waitlist Control.** Participants randomized to WLC will remain on the waitlist for their treatment of choice but receive the same emergency naloxone kit and monthly assessments as IBT participants. WLC participants will not receive the daily IVR calls and bi-monthly visits described above. Brief comment is warranted on the potential for assessment reactivity to confound group comparisons if there is uneven contact between IBT and WLC groups. One such concern is if the assessments inadvertently function as an intervention, thereby improving the outcomes in the control group and obscuring the effect of the intervention. We saw no evidence in our R34 that completion of monthly assessments inflated biochemically-verified abstinence outcomes in the WLC group (which were 0% at all timepoints), and this is also consistent with a recent study by Co-I [name] showing no reactivity associated with technology-assisted monitoring of alcohol use (Fazzino et al., 2016). Another possibility is that the IVR calls and bi-monthly visits contribute to the IBT outcomes. As these components are part of the IBT intervention rather than assessments of outcome, this would not be a problem. While we think it is unlikely that simply calling participants daily (without BUP) could produce the abstinence rates seen in our pilot study, this is an empirical question that can be evaluated in a future study to dismantle IBT to evaluate the contribution of its individual components. Overall, our aim in the present proposal is to utilize a WLC condition that generally reflects the waitlist conditions received by individuals in the real world, and daily IVR calls and bi-monthly study visits are not a part of the typical waitlist experience.

WLC participants who have not entered treatment by the end of the study will be offered the opportunity to receive the 24-week IBT protocol at that time (see Figure). They will receive the same procedures as outlined above for participants originally randomized to IBT (i.e., BUP induction in Week 1, bi-monthly visits and computerized BUP dispensing thereafter). They will receive all other IBT components (e.g., IVR-generated daily monitoring, random call-backs, HIV+Hepatitis and OD education) and complete assessments monthly for 24 weeks.

[figure not shown]

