### Statistical methods

IBT and WLC groups will be compared on baseline characteristics using analyses of variance for continuous and chi-square tests for categorical variables. If characteristics differ significantly and are predictive of outcome, they will be considered as covariates in subsequent analyses. The primary outcome

will be the percent of participants in IBT and WLC conditions with biochemically-confirmed illicit opioid abstinence at the 24-week assessment, evaluated based on a Cochran-Mantel-Haenszel (C-M-H) chi square test with site as the stratification variable. Primary analyses will include all randomized subjects independent of early dropout and with missing urine specimens considered positive for illicit opioids, consistent with an intent-to-treat approach (Armitage, 1983). The Breslow-Day test will be used to test homogeneity of the treatment effects across sites. If applicable, logistic regression will be used to adjust for baseline covariates confounded with treatment group. Though not the primary outcome, abstinence at other monthly assessments will be compared across treatments with Bonferroni-adjusted C-M-H tests to control experiment-wise type I error rate below  $\alpha=.05$ . Within the IBT group, generalized estimating equation (SAS, PROC GENMOD) will be used to characterize the temporal trend in abstinence across assessments. Fixed factors will include recruitment site and the within-subject factor, assessment time, along with their interactions. Repeated measures analyses of variance (SAS, PROC MIXED) will be used to compare groups on continuous outcomes (e.g., past-month frequency of illicit opioid and IV use, ASI subscales, BDI, HIV knowledge, OD risk knowledge). If significant treatment by time interactions are detected, partial F-tests will be used to examine simple effects of treatment at each assessment. Additional repeated measures analyses will characterize temporal patterns in IBT-specific outcomes (e.g., BUP adherence, IVR utilization, satisfaction). For WLC participants who after 24 weeks transition to IBT, estimates of abstinence will be obtained with corresponding 95% confidence intervals at each assessment. Statistical analyses will be performed using SAS V9.4 (SAS Institute, Cary, NC).

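### Trial 2 reports crossover abstinence without reference to each person's Week 24 status, so controls already abstinent can count as abstinent on IBT

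*Supplement*

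**What the plan says.** **Who may cross over.** The sentence "WLC participants who have not entered treatment by Week 24 will be offered the opportunity to cross over to IBT at that time" stands in both protocols, under the survey and questionnaire heading of Methods and Procedures. Trial 2, Waitlist Control, puts it this way: "WLC participants who have not entered treatment by the end of the study will be offered the opportunity to receive the 24-week IBT protocol". Trial 2, Study Design, gives the same single condition.

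**What they receive.** Trial 2, Waitlist Control: "They will receive the same procedures as outlined above for participants originally randomized to IBT (i.e., BUP induction in Week 1". The list goes on to the later visits and the other IBT components, with monthly assessments for 24 weeks. It names no repeat screening.

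**What the data are for.** Both protocols describe the crossover as "contributing additional within-subject data with which to evaluate the efficacy of the IBT intervention". Trial 2, Study Design, adds: "This study design feature will provide additional data with which to evaluate IBT effects beyond the initial randomized sample of 100 participants".

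**How they are analysed.** Trial 2, Statistical methods: "For WLC participants who after 24 weeks transition to IBT, estimates of abstinence will be obtained with corresponding 95% confidence intervals at each assessment". Trial 1, Statistical methods, has no crossover analysis.

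**Entry to the randomised trial.** Inclusion/Exclusion Criteria in both protocols require participants to "provide an opioid-positive urine at study intake". They also require opioid use disorder and good health, and exclude dependence on sedative-hypnotics. Risks/Benefits in both says that buprenorphine in physically dependent people "should not result in acute toxicity because these individuals are tolerant to such drug effects", and lists intake criteria meant to keep out those with too little dependence.

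**The concern.** By rule, everyone in the randomised IBT arm had an opioid-positive urine at entry, so a later negative urine is a change. In the crossover group it need not be. A control who stopped illicit use during the six months without entering treatment meets the only stated condition. If that person's later urines stay negative, each counts as abstinence on IBT although nothing changed.

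The Trial 2 estimate cannot separate these people from those who became abstinent after starting IBT. A stand-alone percentage is also not a within-subject result. At stake is how a supportive efficacy figure is read, particularly if it is set beside the abstinence rate of the randomised IBT arm.

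A second, smaller matter is that the documents do not say whether the entry criteria are looked at again before crossover induction. The safety argument in Risks/Benefits speaks of dependent and tolerant people, a state that is documented only at intake.

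**Working it through.** **Inputs**
- Planned Week 24 abstinence: 60% IBT and 15% WLC (Sample size justification, both trials).
- Pilot WLC abstinence: 0% at all timepoints (Trial 2, Waitlist Control).
- q, the share of crossovers already negative at Week 24: not given. Values of 0%, 5%, 15% and 30% are assumed.
- p, abstinence after crossover among those still positive at Week 24: not given. The plan's 60% is used, with 40% as a less favourable case.
- Already-negative people are assumed to stay negative.

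**The plan's own figure.** The documents give no figure for the crossover. The power statement that contains the 60% and 15% claims more than 95%. A two-sided test of two proportions at alpha .05 (two-sided is assumed) gives 99.9% at 50 per arm and above 99.9% at 100 per arm, the sizes for which the statements were written. The claim reproduces, and nothing in it uses crossover data.

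**Size of the distortion.**
- Reported crossover abstinence = q + (1 − q) × p
- Excess over p = q × (1 − p)
- Paired change from Week 24 = reported value − q = (1 − q) × p

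For q = 15% and p = 60%:
- reported: 0.15 + 0.85 × 0.60 = 0.66
- excess: 0.15 × 0.40 = 0.06
- paired change: 0.66 − 0.15 = 0.51

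| q | p = 60%: reported | excess (points) | paired change (points) | p = 40%: reported | excess (points) | paired change (points) |
|---|---|---|---|---|---|---|
| 0% | 60% | 0 | 60 | 40% | 0 | 40 |
| 5% | 62% | 2 | 57 | 43% | 3 | 38 |
| 15% | 66% | 6 | 51 | 49% | 9 | 34 |
| 30% | 72% | 12 | 42 | 58% | 18 | 28 |

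The reported percentage rises with q and the paired change falls with q. The analysis written for Trial 2 therefore errs in IBT's favour, and the within-person comparison that the protocol describes would not.

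**Against the precision.** With an assumed 25 crossovers at 60%, the 95% half-width is 1.96 × √(0.60 × 0.40 / 25) = 0.19, about 19 points.

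**Missing Week 24 urines.** The primary analysis counts a missing specimen as positive. Applied to a crossover baseline, that rule would turn a missing Week 24 urine followed by a negative one into an improvement. It cannot simply be carried over. The summaries of changes allow samples to be omitted for COVID-19 reasons, so some gaps are likely.

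**The case against.** **No main result depends on this.** The primary outcome in both trials is measured at Week 24, before any crossover, and no test or power statement uses crossover data. A reader might infer that the primary comparison is biased, but the documents give no support for that. This objection stands in full.

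**Only Trial 2 writes the analysis.** A reader might say that both trials count already-abstinent controls as IBT successes. Trial 1 states a use for the data but specifies no analysis. Trial 2's estimate is separate, and is neither pooled with nor tested against the randomised arm. This stands, and limits the point to one descriptive estimate.

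**The 15% is not a forecast for crossovers.** It is a planning rate for the whole control arm, described as conservative, and it includes people who entered treatment and so are not offered crossover. The only observed control rate is the pilot's 0%. It is tempting to compute 0.15 × 25 = 3.75 expected negatives and 1 − 0.85^25 = 98% for at least one, but those figures describe all controls in an arm of assumed size, not crossovers. The table therefore gives a range.

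**The bias is within the noise.** Six points is well inside a half-width of 19. True, but the excess has a known direction and does not shrink with more participants, and the urine needed to remove it is already scheduled.

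**Silence on re-screening is not contradiction.** A reader might infer that the crossover rule contradicts the stated basis for safe induction. The documents do not go that far. Crossover is an offer; Week 1 dosing is individually adjusted at daily visits; pregnancy ends participation; and investigators may terminate participation for danger. The Week 24 visit is an abbreviated intake with urinalysis, and one negative urine does not show that dependence or the disorder has gone. What remains is that the premise is left unverified at crossover, because no written rule says which criteria are re-checked.

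**Conclusion.** The point holds for Trial 2's crossover estimate. As written, it is a one-sample percentage without a baseline, offered as additional and within-subject evidence of efficacy, in a group whose only stated entry condition is not having entered treatment. It may be inflated by 0 points at the pilot's control rate, 2 points if 5% of crossovers are already negative and 6 points if 15% are. With 40% conversion in place of 60%, the last two become 3 and 9 points. These figures assume that people already negative stay negative, and the true share among crossovers is unknown.

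The randomised Week 24 comparison is unaffected. In Trial 1 the point applies only if its crossover data are used as that protocol says. On re-screening, the finding is an unreconciled gap between sections, not a contradiction.

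**What to change.** **Analysis (Trial 2, Statistical methods).**
- Define the scheduled Week 24 urine as the crossover baseline.
- Replace the stand-alone estimate with a paired within-person comparison against Week 24 status at each later assessment (for example a paired difference in proportions with its 95% confidence interval), or add that comparison.
- Show abstinence separately for those positive and those negative at Week 24.
- State how a missing Week 24 urine is handled, without simply reusing the missing-is-positive rule.
- Label the result as uncontrolled and drawn from a selected group. A paired change still cannot separate IBT from time or from month-to-month fluctuation in use.

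Making the opioid-positive stratum the headline figure is one acceptable choice, but not required. Add the same text to Trial 1, Statistical methods, if its crossover data are to be used.

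**Reconciliation (both protocols).** Bring the crossover text into line with Inclusion/Exclusion Criteria and with the dependence safeguard in Risks/Benefits by stating whether, and which, entry criteria are re-checked before crossover induction. Which clinical rule applies is for the investigators.

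**Cost.** A few lines of analysis text, no new visits or specimens, and less precision within small strata.

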**Statistical methods.** IBT and WLC groups will be compared on baseline characteristics using analyses of variance for continuous and chi-square tests for categorical variables. If characteristics differ significantly and are predictive of outcome, they will be considered as covariates in subsequent analyses. The primary outcome will be the percent of participants in IBT and WLC conditions with biochemically-confirmed illicit opioid abstinence at the 24-week assessment, evaluated based on a chi square test. Primary analyses will include all randomized subjects independent of early dropout and with missing urine specimens considered positive for illicit opioids, consistent with an intent-to-treat approach (Armitage, 1983). We hypothesize that participants receiving IBT will achieve significantly greater biochemically-verified illicit opioid abstinence relative to WLC. If applicable, logistic regression will be used to adjust for baseline covariates confounded with treatment group. Though not the primary outcome, abstinence at the other monthly assessments will be compared between groups with Bonferroni-adjusted chi square tests to control experiment-wise type I error rate below  $\alpha=.05$ . Within the IBT group, generalized estimating equation (SAS, PROC GENMOD) will be used to characterize the temporal trend in abstinence across monthly assessments. Additional outcomes will include IV opioid use, other (non-opioid) drug use, retention, BUP adherence, IVR utilization, and patient satisfaction. Repeated measures analyses of variance (SAS, PROC MIXED) will be used to compare groups on continuous outcomes (e.g., past-month frequency of illicit opioid and IV use, ASI subscales, BDI, HIV+HCV knowledge). If significant treatment by time interactions are detected, partial F-tests will be used to examine simple effects of treatment at each assessment. Additional repeated measures analyses will characterize temporal patterns in IBT-specific outcomes (e.g., BUP adherence, IVR utilization, satisfaction). Statistical analyses will be performed using SAS statistical software Version 9.4.

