**Sample size justification.** The proposed sample size is based on having sufficient power for detecting treatment differences for both primary and secondary outcomes. Regarding the primary outcome measure, the percent of participants negative for illicit opioids at the 24-week assessment, power is estimated to be greater than 95% using  $\alpha=.05$  if true abstinence rates are as low as 60% vs. 15% for IBT and WLC groups, respectively. These estimates are more conservative than our R34 outcomes, with lower abstinence predicted in IBT as we increase the duration to 24 weeks. Furthermore, power is estimated to be 80% or more to detect group differences as low as 30% in 24-week abstinence rates ( $ES=0.56$ ). For secondary outcomes, effect sizes range from small to moderate. The estimated mean

differences and minimum detectable effect sizes corresponding to 80% power ( $\alpha=.05$ ) for detecting treatment group differences in the change from baseline to Week 24 for representative ASI subscales are: Employment=.118 (ES=0.32), Psych=.107 (ES=0.51), Legal=.062 (ES=0.45), and Drug=.079 (ES=0.72). Similarly, power is 80% for detecting a mean difference of 5.5 units in the 24-week change in BDI (ES=0.42), which is smaller than we observed in our pilot trial. Lastly, power is estimated to be 80% to detect a mean absolute difference of 8.5% in the pre-post change in HIV knowledge scores (ES=0.54). It should be noted that these effect sizes (Cohen d's) are expressed relative to the between-subject variability at baseline [i.e.  $(\Delta_{IBT}-\Delta_{WLC})/\sigma_{\text{between-subject}}$ ], not the variability in the change scores [i.e.  $(\Delta_{IBT}-\Delta_{WLC})/\sigma_{\Delta}$ ] (Becker, 1988; Morris, 2008). The actual computation accounts for the correlation observed across repeated assessments for each outcome observed in our pilot data which is responsible for the different estimates of detectable ES's.

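### The Bonferroni rule for the five earlier monthly abstinence tests controls error for those five only, not experiment-wise, and Holm would give the same control with more power

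*Supplement*

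**What the plan says.** In the Trial 1 protocol (Statistical Considerations, Statistical methods) the primary outcome is "illicit opioid abstinence at the 24-week assessment, evaluated based on a chi square test". The sample size justification powers that test at the whole of α = .05: power is "greater than 95% using $\alpha=.05$ if true abstinence rates are as low as 60% vs. 15" per cent.

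The other visits have their own sentence, which begins: "Though not the primary outcome, abstinence at the other monthly assessments will be compared between groups". The stated method for this comparison works "with Bonferroni-adjusted chi square tests to control experiment-wise type I error rate below" a level of .05. Assessments fall "at Weeks 4, 8, 12, 16, 20, and 24", so there are five of these other tests.

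The Trial 2 protocol (Statistical methods) has the same rule for its stratified test: "with Bonferroni-adjusted C-M-H tests to control experiment-wise type I error rate below" .05.

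Neither protocol gives the Bonferroni divisor, says whether Week 24 belongs to the family, or makes the monthly tests depend on the Week 24 result.

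**The concern.** Experiment-wise error is normally understood as the chance of at least one false positive among all the tests of the experiment, and here that would include the primary. Week 24 already uses .05. If the five earlier visits share a further .05 and are tested whatever Week 24 shows, the six tests together are not held below .05. A reader of the report could take an earlier-month result, shown beside a failed Week 24, to be protected across the whole trial when it is protected only within the set of five.

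There is also a question of efficiency. Single-step Bonferroni asks every earlier visit to pass .01. Showing abstinence at each of several visits is relevant to the stated objective of whether the effect lasts. The Trial 1 target has since been changed to 50 in total, and Trial 2 was reduced to align with it (each protocol's summary of changes), so power at these visits is no longer ample.

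**Working it through.** **Inputs from the documents.** Week 24 is tested at α = .05. There are five other monthly tests with a Bonferroni target of .05. The original Trial 1 plan has 50 per arm; the changed target is 50 in total.

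**Assumptions.** Divisor 5 (6 shown as the alternative); two-sided tests; 1:1 allocation, hence 25 per arm; correlation between visits not given, so a range is shown.

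**1. The primary uses the full two-sided .05.** The plan's detectable effect size of 0.56 at 80% power follows from (1.960 + 0.842) × √(2/50) = 2.802 × 0.200 = 0.560. Power for 60% vs 15% at 50 per arm and two-sided .05 is 99.9%, consistent with the stated figure above 95%.

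**2. The plan's error statement, for the five tests it names.** Each is at .05/5 = .01.
- Bound: 5 × .01 = .050.
- If independent: 1 − .99⁵ = .049.

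The stated control reproduces for these five.

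**3. The same statement with Week 24 counted.**
- Divisor 5, bound: .05 + 5 × .01 = .100. If independent: 1 − .95 × .99⁵ = .0966.
- Divisor 6, bound: .05 + 5 × (.05/6) = .0917. If independent: .0889.

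**4. Effect of correlation** (simulated normal statistics, no effect at any visit, divisor 5, chance of any false positive among six):

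| Correlation between tests | Equal at all pairs | Decaying with time (AR(1)) |
|---|---|---|
| 0 | 9.7% (exact) | 9.7% (exact) |
| .5 | 8.2% | 9.0% |
| .8 | 6.2% | 7.4% |
| .9 | 5.4% | 6.3% |
| 1 | 5.0% | 5.0% |

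The range is therefore about 5% to 10%.

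**5. Separating multiplicity from small-sample size.** Simulating uncorrected Pearson chi-square tests on binary data at 25 per arm (latent correlation .5, common abstinence 15%, 30%, 50%), the six-test rate is about 9.6%, 9.6% and 10.3%. Week 24 alone then runs at about 5.4%, 5.4% and 6.5%, and the five other tests together at 4.6–4.8%. Part of the total is thus the size of the chi-square approximation in small arms, which is a different matter.

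**6. Holm against Bonferroni over the same five tests, no gate on Week 24.** Holm compares the smallest p-value with .05/5, the next with .05/4, and so on to .05/1, stopping at the first failure. It rejects whatever Bonferroni rejects, and sometimes more. In the no-effect simulations of step 5 the chance of any false positive among the five was the same for both. Power at 25 per arm, latent correlation .5:

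| Assumed abstinence, IBT vs WLC | Per month: Bonferroni → Holm | All five months: Bonferroni → Holm |
|---|---|---|
| 60% vs 15% at every visit | 0.81 → 0.90 | 0.47 → 0.76 |
| 45% vs 15% at every visit | 0.41 → 0.50 | 0.06 → 0.22 |
| 85, 80, 70, 60, 50, 40% vs 15% | gains at every visit (Week 20: 0.56 → 0.78) | 0.48 → 0.75 |

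**7. Gating the five tests on a significant Week 24, then Holm.** This holds all six at a nominal .05. In the declining pattern, however, Week 24 power is about 0.53, so power at Weeks 4 to 20 falls from 0.998–0.56 under the plan to about 0.53–0.45. At 45% vs 15% it falls slightly, from 0.41 to 0.39 per month.

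**The case against.** The sentence opens by setting the primary apart and applies Bonferroni only to the remaining visits. A single primary at full alpha beside a separately controlled secondary family is a usual design. On that reading the arithmetic is right, the word experiment-wise is merely loose, and Bonferroni is a valid if conservative choice. Week 24 is plainly the sole primary, so an earlier-month result could not be presented as primary success. Most of this stands: the design is acceptable, and what fails is the label.

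A reader might go further and infer that the plan runs at about 8–10% error. The documents do not fix that figure. It needs no effect at any visit, an assumed divisor, and low to moderate correlation. The same people are tested repeatedly with "missing urine specimens considered positive for illicit opioids", so dropout carries forward and correlation may well be high, which pulls the rate towards 5%.

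A reader might also infer that the monthly tests must be made conditional on Week 24. That is a trade-off, not a correction. The pilot showed abstinence falling from 88% to 68% over 12 weeks, and the plan itself predicts lower abstinence at 24 weeks, so a gate placed on what may be the weakest visit could cost heavily at the earlier ones.

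The argument that Holm is only a matter of taste does not stand. It has the same error guarantee and needs no added assumption.

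**Conclusion.** The point holds in limited form and is minor. The stated control below .05 is true of the five non-primary abstinence tests and untrue of the experiment once Week 24 is counted: the bound is .10 (.092 with a divisor of six), and the likely rate is anywhere from about 5% to 10%, because the correlation is not stated. Nothing here inflates the error rate of the Week 24 test or calls its result into question.

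The choice of single-step Bonferroni gives up power for no gain in error control. The size of that loss rests on 25 per arm, latent correlation .5 and illustrative abstinence rates; its direction does not, since Holm can never reject less. The power figures are for Trial 1's unstratified chi-square test. The same logic applies to the C-M-H tests in Trial 2, which were not simulated.

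**What to change.** In Trial 1, Statistical methods, replace the Bonferroni sentence with wording such as: *Abstinence at Weeks 4, 8, 12, 16 and 20 will be compared between groups with Holm-adjusted chi-square tests at a family level of .05. This controls the family-wise error rate for these five secondary comparisons, separately from the Week 24 primary test at two-sided .05.* In Trial 2, make the same change with C-M-H tests stratified by site. Drop the term experiment-wise in both.

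The cost is one sentence per protocol, with no extra data and no change to the primary.

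If the sponsor wants all six tests held at .05, gating on Week 24 achieves it without touching the primary's alpha. It should be chosen knowingly: the earlier months become descriptive whenever Week 24 fails, and power there can fall sharply if abstinence declines by Week 24.
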